## Abstract

**Background:**

Diabetes specific emotional problems interfere with the demanding daily management of living with type 2 diabetes mellitus (T2DM). Possibly, offering direct feedback on diabetes management may diminish the presence of diabetes specific emotional problems and might enhance the patients' belief they are able to manage their illness. It is hypothesized that self-monitoring of glucose in combination with an algorithm how and when to act will motivate T2DM patients to become more active participants in their own care leading to a decrease in diabetes related distress and an increased self-efficacy.

**Methods and design:**

Six hundred patients with T2DM (45 ≤ 75 years) who receive care in a structured diabetes care system, HbA1c ≥ 7.0%, and not using insulin will be recruited and randomized into 3 groups; Self-monitoring of Blood Glucose (SMBG), Self-monitoring of Urine Glucose (SMUG) and usual care (n = 200 per group). Participants are eligible if they have a known disease duration of over 1 year and have used SMBG or SMUG less than 3 times in the previous year. All 3 groups will receive standardized diabetes care. The intervention groups will receive additional instructions on how to perform self-monitoring of glucose and how to interpret the results. Main outcome measures are changes in diabetes specific emotional distress and self-efficacy. Secondary outcome measures include difference in HbA1c, patient satisfaction, occurrence of hypoglycaemia, physical activity, costs of direct and indirect healthcare and changes in illness beliefs.

**Discussion:**

The IN CONTROL-trial is designed to explore whether feedback from self-monitoring of glucose in T2DM patients who do not require insulin can affect diabetes specific emotional distress and increase self-efficacy. Based on the self-regulation model it is hypothesized that glucose self-monitoring feedback changes illness perceptions, guiding the patient to reduce emotional responses to experienced threats, and influences the patients ability to perform and maintain self-management skills.

**Trial registration:**

Current Controlled Trials ISRCTN84568563

## Background

Diabetes specific emotional problems can interfere with the strict regime type 2 diabetes mellitus (T2DM) demands. Emotional problems, such as not accepting diabetes, fear for hypoglycaemia and worrying about complications, might impact aspects of quality of life, for example, increase diabetes related distress, which in turn might affect self-care behaviours and glycaemic control [1,2]. Diabetes self-management can protect against the development of diabetes specific distress [3] and it can have a positive effect on perceived self-efficacy [4]. Possibly, common self-management factors such as guidance in accepting diabetes, formulating clear and concrete goals [3] as well as personal confidence and belief in the ability to recognize, understand and act on symptoms related to T2DM may be helpful in reducing levels of distress [5]. An example of a self-management method is glucose self-monitoring. Based on collecting data of glucose levels on different time-points, self-monitoring and its feedback might help patients to a better understanding of day to day variation in glucose levels. With the self-monitoring information, lifestyle adjustments can be made, provided the patient is informed how to interpret the results and what actions to take.

The hypothesis that self-monitoring of glucose empowers the patient by its feedback is based on the principles of Leventhal's self-regulation model [6,7]. This model proposes that individuals construct schematic perceptions of illness and health-threatening conditions according to sources of information that are available to them. These illness perceptions determine how patients respond when confronted with their illness or related threats and are mediators in the willingness and ability to take action. Feedback on the illness condition allows adaption of illness perceptions, which lead to changes in self-efficacy and illness specific distress.

### Previous research

To date, research in self-monitoring of glucose has primarily focused on reaching and maintaining glycaemic control. Therefore, up to now the evaluation of success or failure of self-monitoring has been based upon its ability to decrease HbA1c to normal values.

Self-monitoring of glucose has been proven successful in regulating HbA1c in patients with type 1 diabetes [8] and T2DM requiring insulin [9]. For T2DM patients not using insulin this is still a matter of debate [10-12]. Meta-analyses on self-monitoring of blood glucose (SMBG) in T2DM not using insulin revealed small effects on HbA1c [13-15]. The improvements shown were clinically relevant and statistically significant. Nevertheless, in all reviews the methodological quality of the studies included was questioned. The recently well-designed DiGEM trial addressed most of the methodological comments on the previous studies and found no effects on glycaemic control in T2DM patients not requiring insulin [16].

Before the widespread extent of SMBG, self-monitoring of urine glucose (SMUG) was used to indicate episodes of hyperglycaemia during the corresponding urine excretion time. Even though urine glucose excretion is influenced by renal threshold, SMUG can provide basic information on glycaemic status. Furthermore, feedback derived from SMUG can motivate T2DM patients to become actively engaged in self-management of T2DM [17], irrespective of the monitoring technique. Nevertheless, it is unknown if SMUG provides enough feedback to influence illness perceptions and subsequently diminish diabetes related distress.

Whether self-monitoring of glucose can help patients to better understand their diabetes and to an increased self-efficacy and less diabetes related distress is not known and has not been investigated as a primary objective yet. Information from qualitative research suggest that self-monitoring of glucose may have a negative impact regarding aspects of quality of life and patient-satisfaction [18-20]. Possibly, insufficient knowledge in how and when to perform and interpret SMBG might lead to these results.

In this trial the effect of self-monitoring of glucose regarding diabetes-specific distress and self-efficacy in combination with education in self-monitoring and an algorithm what to do is evaluated.

### IN CONTROL Objectives

The aim of the study is to assess the effects of SMBG and SMUG in patients with type 2 diabetes who are not using insulin compared to usual care. Primary outcome measures are changes in diabetes specific emotional distress and self-efficacy. Secondary outcomes are changes in glycaemic control, patient treatment satisfaction, physical activity, health status, status of depression, occurrence of hypoglycaemia, cost-effectiveness and cost-utility. As part of a process evaluation changes in illness perceptions, perceived severity and social support are determined as well.

## Methods

### Design of the study

"IN CONTROL" entails a 3-armed randomized clinical trial performed in the province of Noord-Holland, The Netherlands. The Medical Ethical Committee of the VUmc approved the study design, protocols, information letters to the patients and informed consent form.

### Setting

The participating diabetes care systems provide and manage regional diabetes care in addition to the care of general practitioners and their nurse practitioners. All care systems are based on the chronic care model [21-23] and coordinate regional diabetes care using a centrally organized database which is available for all involved caregivers. Each patient is annually invited for a physical examination and a visit with a diabetes nurse and a dietician for information, education and advise. This visit includes assessment and discussion of glucose control and the presence of complications. If necessary, follow-up visits are scheduled. The results of the visits are sent to the patients' general practitioner (GP) who is responsible for the management of the patients.

### Study population

In total 600 consenting participants will be recruited. Patients are considered eligible if they are diagnosed with T2DM and meet the following criteria:

❑ known disease duration of over 1 year

❑ recent HbA1c ≥ 7.0%

❑ treated with diet and/or oral hypoglycaemic agents

❑ do not require insulin at inclusion

❑ aged between 45 and 75 years

❑ used SMBG or SMUG less than 3 times in the previous year

Participants will be randomly assigned to one of the following 3 groups (figure 1):

**Figure 1 F1:**
[figure not shown]
**Design of the RCT**.

❑ intervention group A, performing SMBG with specific SMBG education, in addition to usual diabetes care provided by the regional diabetes care system.

❑ intervention group B, performing SMUG with specific SMUG education, in addition to usual diabetes care provided by the regional diabetes care system.

❑ control group receiving usual diabetes care provided by the regional diabetes care system.

### Randomization

For intervention allocation a randomization list is drawn up using a computerized randomization computer program (Random Allocation Software version 1.0.0). As different effects may be expected of prescribed drug treatments that are likely to cause hypoglycaemia, for example sulfylureas or glinides (SU), randomization will be pre-stratified by treatment (using SU or not (Non-SU)). A research-manager, who is not involved in the patients care, allocates the patient to one of the 3 groups by using the randomization list. Intervention allocation will be concealed for the principal investigator who is responsible for the data analyses. Participants may withdraw from the study at their own request and without providing reasons. Date of withdrawal will be recorded and effort will be made to contact participants lost to follow up. Only participants withdrawn prior to randomization will be replaced.

### Intervention groups (SMBG & SMUG)

Following randomization participants allocated to one of the intervention groups receive a training in SMBG or SMUG delivered by trained research assistants and a flowchart with instructions when to perform and how to interpret self-monitoring. After this training participants should be able to perform SMBG or SMUG and interpret the results, identify factors that can influence glucose level and identify when additional tests are needed.

The acquired skills in self-monitoring are checked and if necessary corrected in a control visit of maximal 30 minutes, 7 to 14 days after randomization. During this visit a stepwise script outlining the self-monitoring skills needed is used. All participants in the SMBG group are requested to measure their blood glucose twice a week (one weekday, one weekend day) at 6 different time points a day (fasting, 1 1/2 – 2 hrs after breakfast, before lunch, 1 1/2 – 2 hrs after lunch, before diner, before bedtime) with a glucose-meter (LifeScan OneTouch^® ^Ultra^®^2). Participants in the SMUG group are requested to test their urine twice a week (one weekday, one weekend day) in the evening after dinner (Urispec™ plus urine glucose in vitro reagent test strips). Both groups will receive a diary in which they have to record the obtained values for blood or urine glucose. To avoid extra psychological burden we allow participants to adjust self-monitoring to a frequency 'they feel comfortable with' starting from 2 months after baseline until the end of the study.

### Measurements

Outcome measures are obtained at baseline, 4 and 12 months. These are collected by self-administered questionnaires, blood sampling and anthropometry. Diabetes specific distress is assessed by the Problem Areas In Diabetes scale (PAID) [24,25] and self-efficacy by the Confidence In Diabetes Self-care questionnaire (CIDS) [26] adjusted for T2DM. Patient treatment satisfaction is assessed by the Diabetes Treatment Satisfaction Questionnaire (DTSQ) [27], physical activity is assessed by the short International Physical Activity Questionnaire (IPAQ-7) [28], health status and cost utility are assessed with the Euroqol-5D [29-31]. Status of depression is assessed at baseline and at 12 months using the Patient Health Questionnaire-9 (PHQ-9) [32], Demographic variables on age, gender, diabetes duration, marital status and level of education are assessed at baseline by means of a self-administered questionnaire. Glycaemic control is measured by HbA1c-level. Furthermore, BMI and blood-pressure are measured. Participants are asked to register occurrence of hypoglycaemia in care-diaries. Costs of direct health care and indirect non-healthcare will be inventoried in cost-diaries and recorded in 3-monthly intervals. Table 1 summarizes the measures and their timing.

**Table 1 T1:** Study measures

**Measures**	**Baseline**	**2 months**	**3 months**	**4 months**	**6 months**	**9 months**	**12 months**

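### Hypoglycaemia is compared between arms from participants' diaries, but only the SMBG arm has a study blood glucose meter, so the comparison is open to detection bias

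*Protocol article*

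**What the plan says.** The protocol article's objectives list "occurrence of hypoglycaemia, cost-effectiveness and cost-utility" among the secondary outcomes of SMBG and SMUG compared with usual care. The Measurements section gives the method of collection: "Participants are asked to register occurrence of hypoglycaemia in care-diaries". It states no glucose threshold, symptom criterion or confirmation rule.

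The section on the intervention groups describes different monitoring by arm:

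- **SMBG:** "All participants in the SMBG group are requested to measure their blood glucose twice a week", on one weekday and one weekend day, at six time points each day, "with a glucose-meter (LifeScan OneTouch" Ultra 2).
- **SMUG:** "Participants in the SMUG group are requested to test their urine twice a week (one weekday, one weekend day) in the evening after dinner". The Background describes urine testing as a way to show episodes of high glucose.
- **Usual care:** no study self-monitoring.

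A separate diary for readings goes to the two intervention arms: "Both groups will receive a diary in which they have to record the obtained values for blood or urine glucose". From 2 months after baseline, participants may set their own monitoring frequency. At entry all had self-monitored fewer than 3 times in the previous year.

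The Analyses section compares the intervention groups with usual care with 95% confidence intervals, and applies linear or logistic regression to each outcome.

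**The concern.** In the SMBG arm the allocated intervention is also an instrument for detecting the outcome. A participant with a meter can see a low value that causes no symptoms and register it. A participant testing urine, or not testing, cannot. Randomisation does not remove this, because the difference arises after allocation. Concealing allocation from the analyst does not remove it either, because the difference enters when the participant writes the entry.

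The risk is a difference in recorded hypoglycaemia between SMBG and usual care that reflects detection and not occurrence, reported as an effect of self-monitoring. The same problem affects any contrast of SMBG with SMUG. The contrast of SMUG with usual care is free of it, since neither arm has a study meter.

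**Working it through.** The plan states no hypoglycaemia rate and no power for this outcome, so there is no figure of its own to reproduce. The check has three steps.

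**1. Detection opportunities.** From the section on the intervention groups: 2 days × 6 time points = 12 blood readings a week under SMBG. Two months is 2 × 52/12 ≈ 8.7 weeks, so 12 × 8.7 ≈ 104 scheduled readings. The study schedules 0 blood glucose self-tests in the other two arms. After 2 months the number is unknown, because frequency is self-chosen.

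**2. Illustration with equal true risk.** Assumptions, none of them from the article:

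- A proportion p0 of every arm records at least one symptomatic episode (5%, 10% or 20%).
- Among the remaining SMBG participants, a proportion a records a low found only by the meter (2%, 5% or 10%).

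The recorded proportion under SMBG is p1 = p0 + (1 − p0) × a, and the spurious risk ratio is p1/p0.

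The chance of a significant excess under SMBG is approximately Φ[(p1 − p0 − 1.96 × SE0)/SE1]. SE0 is the pooled and SE1 the unpooled standard error, two-sided α is 0.05, and there are 200 × 0.85 = 170 completers per arm (the article's 200 per group and 15% drop-out). Without bias this chance would be about 2.5%.

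Worked case, p0 = 5% and a = 5%: p1 = 0.05 + 0.95 × 0.05 = 0.0975, and the ratio is 0.0975/0.05 = 1.95. SE0 = 0.0284 and SE1 = 0.0282, so the chance is Φ[(0.0475 − 0.0556)/0.0282] ≈ 39%.

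| p0 | a | p1 | Risk ratio | Chance of significant excess |
|---|---|---|---|---|
| 5% | 2% | 6.9% | 1.38 | 11% |
| 5% | 5% | 9.8% | 1.95 | 39% |
| 5% | 10% | 14.5% | 2.90 | 84% |
| 10% | 2% | 11.8% | 1.18 | 8% |
| 10% | 5% | 14.5% | 1.45 | 24% |
| 10% | 10% | 19.0% | 1.90 | 66% |
| 20% | 2% | 21.6% | 1.08 | 6% |
| 20% | 5% | 24.0% | 1.20 | 14% |
| 20% | 10% | 28.0% | 1.40 | 41% |

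The chance per reading needed to reach these values of a is small. With independent readings, the probability of at least one low in 104 is 1 − (1 − q)^104. This gives 5.1% for q = 0.05% and 9.9% for q = 0.1%.

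**3. The opposite mechanism.** Suppose the meter also leads SMBG participants to discard a fraction f of symptomatic episodes that other arms would register. Then p1 = p0(1 − f) + [1 − p0(1 − f)] × a.

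- p0 = 20%, f = 50%, a = 5%: p1 = 0.10 + 0.90 × 0.05 = 0.145, ratio 0.73.
- p0 = 10%, f = 50%, a = 10%: p1 = 0.05 + 0.95 × 0.10 = 0.145, ratio 1.45.

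The sign of the net bias therefore depends on quantities that the article does not give.

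**The case against.** The strongest reply is that the article does not say what counts as an episode. The request to register hypoglycaemia is addressed to participants in all arms, and the diary of glucose values is described separately. Nothing shows that a low value in that diary becomes an event. The event definition may stand in the full protocol, which is not shown. If the care-diary asks only for symptomatic episodes, most of the bias disappears. This lowers certainty. It does not remove the point, which concerns unequal detection and not a missing definition: any rule that admits meter-only lows is unequal across arms, and the plan as described does not exclude them.

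A reader might infer that SMBG is bound to show more hypoglycaemia. That holds for measured lows. For all recorded episodes it does not, because a meter can refute symptoms, as the ratio of 0.73 shows.

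A reader might also multiply 12 readings by 52 weeks, or apply a per-reading rate of lows to predict extra episodes per participant. The first ignores the free choice of frequency after 2 months. The second needs a rate that the article does not supply.

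Nor does the text support calling this the trial's only safety-related outcome, or the reason for stratifying by sulfonylurea or glinide use. The article is also concerned with distress caused by monitoring, which its primary distress scale addresses. It justifies the stratification by different expected effects between drug groups, and applies it to all outcomes.

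The absence of hypoglycaemia from Table 1 carries little weight. The Measurements text says how it is collected, and a running diary has no fixed visit.

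**Conclusion.** The point stands as a risk of detection bias in one secondary outcome. The unequal detection follows from the text: diary self-report, a study meter in one arm only, comparison with usual care, and no stated restriction to events that every arm can notice. The net direction is probably towards more recorded events under SMBG, but this is not certain.

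The size is not derivable from the article. Under equal true risk, with the assumed 5% to 20% symptomatic and 2% to 10% meter-only proportions and no refuted symptoms, the spurious risk ratio runs from about 1.1 to 2.9. At the low end the effect is minor. At the high end it could by itself produce a significant difference. The primary outcomes (distress and self-efficacy) and the sample size are unaffected. The change is worth making before data collection, because how an episode was noticed cannot be recovered reliably afterwards.

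**What to change.** Keep the care-diary and use the same form in all three arms. Have each entry mark three things: whether the episode was symptomatic, whether help from another person was needed, and whether it was found only by a meter reading.

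Base the between-arm comparison on symptomatic episodes, whether or not a meter confirmed them, and on episodes needing help. Report asymptomatic meter-only lows descriptively for the SMBG arm and leave them out of the comparison. Retaining symptomatic episodes regardless of confirmation limits the effect of refutation by the meter.

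Keeping the diary is preferable to asking at the 4- and 12-month questionnaires, which would replace recording at the time with recall over up to 8 months.

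The cost is one or two extra diary items and fewer countable events. Some difference in reporting will remain, because participants know their arm and those with a meter can check their symptoms.

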***Physiological***							
BMI	X			X			X
Blood pressure	X			X			X
HbA1c	X			X			X
							
***Questionnaires***							
PAID	X			X			X
CIDS	X	X		X	X		X
PHQ-9	X						X
DTSQ	X			X			X
Euroqol-5D	X			X			X
IPAQ-7	X			X			X
							
***Process evaluation***							
IPQ-R subscales	X	X		X	X		X
MDQ subscales	X	X		X	X		X
							
***Costs***							
Cost of medication							X
Cost diaries			X		X	X	X

### Process evaluation and quality assurance

A process evaluation will be performed to evaluate our theories of the processes underlying the effect of self-monitoring. For this evaluation changes in mastery are assessed by the subscales personal control and treatment control of the Revised Illness Perception Questionnaire (IPQ-R) [33] and changes in perceptions of diabetes and social support by the subscales perceived severity and perceived social support from a significant other of the Multidimensional Diabetes Questionnaire (MDQ) [34]. These measures are assessed at 5 time-points (baseline, 2 months, 4 months, 6 months and 12 months) (Table 1).

A script outlining the topics to be covered per visit is used to support the nurses and research assistants in their tasks. Before inclusion all research assistants attend a training in self-monitoring (SMBG and SMUG) and before the start of the intervention their self-monitoring skills are tested in a pilot. During the inclusion period the research assistants are audited. Directly after the training the research assistants are asked about their opinions about their acquired skills in self-monitoring and their capability to train and instruct participants following protocol (5-point Likert scale; 1 = fully disagree, 5 = fully agree). This will also be done after the inclusion period. The participants of the intervention groups are asked to give their opinion on 6 items regarding skills, importance and motivation for self-monitoring at baseline and 2 months after baseline (5-point Likert scale).

### Sample size

The proposed trial is designed to detect a clinically relevant change of self-monitoring of glucose on diabetes specific emotional distress and self-efficacy. No consensus exists about minimal important differences (MID) of diabetes specific distress measured with the PAID and self-efficacy measured with the CIDS. Therefore we set the MID at half a standard deviation [35]. In diabetes patients the standard deviation (SD) of PAID (scores transformed to 0–100) was 20 points [25]. Using a bonferroni correction based on two primary hypotheses with α 0.025 and β 0.15, a sample size of 86 per group is needed to find a difference of 10 points (0.5 SD). Information on the SD of the CIDS is not yet available for T2DM patients. For type 1 diabetes patients the SD of CIDS (scores transformed to 0–100) was 12 points [26]. To detect a decrease of 6 points (0.5 SD), while correcting according to bonferroni based on two primary hypotheses with α 0.025 and β 0.15 a sample size of 86 per group is needed. Taking into account different effects in different treatment groups (SU or non-SU) pre-stratification by treatment will double the sample size. Assuming a 15% drop-out rate, a total of 600 T2DM patients with HbA1c ≥ 7.0% are needed in the study. In addition, with a total of 600 patients it is expected to have sufficient power to detect a clinically relevant decrease of 0.5% in HbA1c.

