### Analyses

On the basis of an intention-to-treat analysis, differences between the intervention groups and usual care group are calculated with 95% confidence intervals. In addition per protocol analyses will be performed. The subgroups SU and non-SU will be analysed separately for all outcome measures. In case there is no effect modification by treatment the data of both subgroups will be pooled. If there are any relevant differences in baseline measurements between the 3 arms, we will adjust the outcomes for these factors (i.e. age, gender, ethnicity, status of depression, diabetes duration, marital status, level of education). Linear and logistic regression will be used to determine the effect of the intervention on each of the outcome measurements. The effect of the intervention will be estimated for sub-groups defined by duration of diabetes, socio-economic status, perceived social support and perceived severity of diabetes, glycaemic control and self-monitoring frequency in order to gain a better understanding as to who benefits most from the intervention. Analyses of moderators and mediators will be performed for the process-evaluation.

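### The sample size splits alpha to 0.025 for two primary outcomes, but the Analyses section reports both arm-versus-usual-care comparisons with 95% confidence intervals and does not carry the split through

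*Protocol article*

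**What the plan says.** All references are to the protocol article.

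- **Objectives** (IN CONTROL Objectives): "Primary outcome measures are changes in diabetes specific emotional distress and self-efficacy". Self-monitoring of blood glucose (SMBG) and of urine glucose (SMUG) are both to be assessed against usual care.
- **Design** (Study population): "Participants will be randomly assigned to one of the following 3 groups", namely SMBG, SMUG and usual care.
- **Planned level** (Sample size): "Using a bonferroni correction based on two primary hypotheses with α 0.025 and β 0.15", which gives 86 per group for a 10-point PAID difference. The same level and the same 86 are given for 6 points on CIDS. The number is then doubled for the SU and non-SU strata and raised for 15% drop-out, to 600 in total.
- **Analysis level** (Analyses): "differences between the intervention groups and usual care group are calculated with 95% confidence intervals". No other level appears there, and the 0.025 is not repeated.
- **Strata** (Analyses): SU and non-SU are analysed separately on every outcome, and pooled if treatment does not modify the effect.
- **Visits** (Measurements): "Outcome measures are obtained at baseline, 4 and 12 months". Table 1 adds CIDS at 2 and 6 months.

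**The concern.** By invoking Bonferroni, the article commits itself to a 5% overall error shared between its primary tests. The analysis text departs from that commitment in two ways.

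1. An interval that matches a test at 0.025 is a 97.5% interval. A reader who judges PAID and CIDS by whether the reported 95% interval excludes zero is testing at 0.05, the level the sample size section had given up.
2. The split counts outcomes only. With two intervention arms each compared with usual care, there are four primary comparisons, and 0.025 on each of four does not hold the total at 5%.

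At stake is the strength of a positive claim. A result with p between 0.025 and 0.05 on one outcome in one arm could be presented as a primary success, although the trial's own planning would not count it.

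**Working it through.** **1. Reproduce the planned figure.** Inputs from the Sample size section: "the standard deviation (SD) of PAID (scores transformed to 0–100) was 20 points" with a difference of 10, and "For type 1 diabetes patients the SD of CIDS (scores transformed to 0–100) was 12 points" with a difference of 6. Both are 0.5 SD. α = 0.025 and power = 0.85.

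n per group = 2(z₁₋α/₂ + z₀.₈₅)² / 0.5²

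- Two-sided 0.025: 2(2.241 + 1.036)² / 0.25 = 85.95, so 86. This matches the article.
- Two-sided 0.05, or one-sided 0.025: 2(1.960 + 1.036)² / 0.25 = 71.8, so 72. This does not match.

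So 86 is a two-sided 0.025 calculation. Total: 86 × 3 arms × 2 strata = 516. Dividing by 0.85 gives 608, and multiplying by 1.15 gives 594; both are close to 600. The arithmetic is sound for its own inputs. With 600 randomised and 15% lost, 510 complete: 170 per arm, or 85 per arm per stratum if the strata are equal.

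**2. Count the comparisons.** 2 outcomes × 2 arms against usual care = 4, at one visit with strata pooled. Separate testing in two strata gives 8.

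**3. Family-wise error with no true effect.** Equal arms sharing one control give a correlation of 0.5 between the two arm comparisons. The PAID–CIDS correlation is not in the document, so a range of 0 to 0.7 is assumed. If all tests were independent, the error would be 1 − (1 − α)ᵏ:

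- k = 4: 1 − 0.95⁴ = 18.5%; 1 − 0.975⁴ = 9.6%.
- k = 2 (one arm, two outcomes): 1 − 0.95² = 9.75%; 1 − 0.975² = 4.9%.

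Simulating correlated normal test statistics gives:

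| Family | At 0.05 (95% CI) | At 0.025 |
|---|---|---|
| 4 comparisons, pooled, one visit | 15–17% | 8–9% |
| 2 outcomes within one arm, pooled, one visit | 8–10% | 4–5% |
| 4 comparisons in each of 2 strata, always tested separately | 28–32% | 15–17% |

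The last row leaves out the article's pooling rule. With the rule included, the 0.05 column falls to about 23–27% for an assumed interaction test at 0.05. It reaches about 30% for one at 0.10. The article gives no threshold.

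**4. Effect of a four-way split (α = 0.05/4 = 0.0125).**

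- Family-wise error over the four pooled comparisons: about 4.0–4.7%.
- Pooled power for 0.5 SD at 170 per arm: about 98%.
- Within-stratum power at 85–86 per arm: about 77% (t-based; 78% by the normal formula), against the stated 85%.
- n to restore 85% within a stratum: 2(2.498 + 1.036)² / 0.25 = 99.9, so 100 per group. That is 600 evaluable, and 600/0.85 = 706 randomised.

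**The case against.** - **The 95% intervals may be for estimation only.** The sentence covers all outcomes and names no significance level, so it does not revoke the 0.025. This stands in part: 0.05 as the decision level is inferred from the intervals. A reader might conclude that the trial has abandoned its correction, and the document does not say so. But the Analyses section then gives no decision level at all for its primary comparisons, and even at 0.025 the four-comparison error is 8–9%.
- **Each arm can be its own family.** SMBG and SMUG use different devices, training and schedules, so this is a defensible convention. Two outcomes at 0.025 would then be correct, at 4–5% within an arm. To call the count of two a plain error would go too far; the article does not say which family it means. The interval mismatch remains on this reading, because 95% intervals give 8–10% within an arm.
- **The strata will usually be pooled.** Under a global null there is no effect modification, so a reader who takes about 31% as the error of the plan as written overlooks the pooling rule. That figure belongs to separate testing in every case.
- **No primary visit is named.** A reader might add the visits to the family and reach higher rates. A condensed article may leave the ranking of visits to the full protocol or SAP, and the extra CIDS visits follow the process-evaluation schedule. This is not counted here as an error.

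**Conclusion.** The point holds in a limited form. The article fixes a Bonferroni level of 0.025 and then gives only 95% intervals for the primary comparisons, so the two sections disagree. The split also leaves the two arm comparisons per outcome uncovered, unless each arm is declared a separate family.

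The mismatch in level breaks 5% control under either definition of the family. Using 0.025 throughout restores control within an arm but not over all four comparisons. These figures rest on one visit, pooled strata, equal arms, an outcome correlation of 0 to 0.7 and, for the 0.05 column, on reading the intervals as tests. Separate SU and non-SU testing adds to the error by an amount that depends on an interaction threshold the article does not give. The stated 86 and 600 are not in question as arithmetic.

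**What to change.** **Minimum.** In Analyses, state that the primary PAID and CIDS comparisons are judged at two-sided 0.025, report them with 97.5% intervals, and say whether each arm is a separate family.

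**Preferred.** Define the confirmatory family as four comparisons (PAID and CIDS; SMBG and SMUG each against usual care) in the pooled strata at one prespecified visit. The article does not indicate which visit; the sponsor must choose it before seeing results by arm. Test with Holm at overall two-sided 0.05 (first step 0.0125). Label stratum-specific and other-visit results as secondary, with unadjusted 95% intervals.

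**Cost.** Primary intervals become slightly wider. If the confirmatory analysis is pooled, this is a wording change with no extra patients. It does, however, make the stratum results secondary, although the sample was doubled for them. If they are to stay confirmatory at 0.0125, the stated 85% power should be restated as about 77%, or the total raised to about 706. That figure covers four comparisons within each stratum; a family of all eight would need a stricter level.
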